**11.5 Safety**

**11.5.1 Adverse events**

All Adverse Events will be recorded on the corresponding page(s) in the Case Report Form. Whenever possible, symptoms should be grouped as a single syndrome or diagnosis. The Investigator should specify the date of onset, intensity, action taken with respect to Investigational Product, corrective treatment/therapy given, outcome and his/her opinion about whether it is possible that the Adverse Event is caused by the Investigational Product.

Laboratory, vital signs or ECG abnormalities will be recorded as Adverse Events only if they are medically relevant: symptomatic, requiring corrective treatment, leading to discontinuation and/or fulfilling a seriousness criterion.

**11.5.2 Serious adverse event**

For serious adverse events, the investigator must immediately take corresponding measures:

Immediately notify the representative of the Monitoring Team, send the signed and dated corresponding pages of in the case report form to the representative of the Monitoring Team, and attach a photocopies of all examinations carried out and the examination dates. For laboratory results, include the laboratory normal ranges. The

contact information (name, address and fax number) of the representative is on the Clinical Trial Protocol. These measures should be completed no later than **24 hours** after SAE.

Care should be taken to ensure that the patient's identity is protected and the patient's identifiers in the Clinical Trial are properly noted on all copies of source documents provided to the Sponsor.

### **11.5.3 Follow-up and risk management**

The Investigator should take all appropriate measures to ensure the safety of the patients.

Screening of subjects should strictly follow the inclusion and exclusion criteria of the study. If an adverse event occurs during the study period, medication will be temporarily discontinued or withdrawn. Relevant evaluations will be performed, including blood routine examination, coagulation, creatinine, hepatic function, renal function, arterial blood gas analysis, ultrasound and computer tomography. Targeted treatment and necessary consultation should be carried out in a timely manner. When dealing with severe adverse events, it is important to make sure patients' airway is clear, respiration, blood pressure and heart rate is steady. Treatment in intensive care unit is recommended when necessary.

Notably, the investigator should follow up the outcome of any Adverse Events (clinical signs, laboratory values or other, etc.) until the patient's condition returns to normal or stabilizes. The follow-up will continue even if the patient withdraws from the clinical trial, and the patient will be interviewed by telephone or face-to-face at the scheduled visit time. The monitoring team may request additional visits and

investigations.

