### **7.6 Temporary/permanent discontinuation of the study drug(s) or loss of follow-up**

The study drug(s) should be continued whenever possible. If the study drug(s) are stopped, it should be determined whether they can be stopped temporarily; permanent study drug(s) discontinuation should be a last resort. Any study drug discontinuation should be fully documented in the CRF. Discontinuation of study medication does not mean discontinuation of follow-up or termination of study participation. In any case, the patient should stay in the study as long as possible.

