### **7.6.1 Temporary treatment discontinuation of the study drug(s)**

If the study drugs must be temporarily discontinued, they should be re-started as soon as possible:

Including the following conditions:

- 1) Severe thrombocytopenia (platelet count <50,000/uL). Patients may restart study

medication once the severe thrombocytopenia resolves;

- 2) Severe bleeding (GUSTO definition);
- 3) Need of treatment with prohibited concomitant medications, see Section 7.5;
- 4) Surgery or procedures associated with major haemorrhage, see Section 7.5.3;

For other surgery or other invasive procedures, study medication may be continued or interrupted temporarily at the discretion of the investigator.

Once the Investigator has considered that the role of the Investigational Product(s) in the occurrence of the event concerned is unlikely and there are no other contraindications to prevent its(their) continued use in the study. Treatment with the Product can be re-initiated under close and appropriate clinical/and or laboratory monitoring.

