### **7.6.2 Permanent treatment discontinuation of the study drug(s)**

- 1) Patient decision. The patient is at any time free to discontinue treatment, without prejudice to further treatment
- 2) Investigator's decision, including but not limited to these examples:
  - ① Pregnancy or desire to become pregnant;
  - ② Incorrectly enrolled patient, violation of the inclusion/exclusion criteria would put the patient at undue risk;
  - ③ Severe non-compliance to study protocol;
  - ④ Adverse events that lead the investigators to believe continued treatment may put the patient at undue risk;
  - ⑤ Clear indication for anticoagulation;

- ⑥ After a temporary withdrawal, the investigator decides that the patient should not restart the study drugs again.

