### **XI. Study risk pre-assessment and risk management**

When subjects take the study drugs, they will be exposed to the risks brought by these drugs, as follows:

1) Side effects of aspirin: bleeding, hematoma, epistaxis, urogenital bleeding, gum bleeding, anemia, hemolysis, blood in urine, indigestion, gastrointestinal and abdominal pain, peptic ulcer and bleeding, kidney injury and acute renal failure, transient transaminase elevation, drug allergy, asthma, urticaria, angioedema or shock, etc.

2) Side effects of ticagrelor: hyperuricemia, hemorrhagic stroke, dyspnea, gastrointestinal bleeding, skin bleeding, urethral bleeding, bleeding at the vascular puncture site, etc.

3) Side effects of clopidogrel: gastrointestinal bleeding, neutropenia, abdominal pain, loss of appetite, gastritis, constipation, skin rash, etc.

Researchers will conduct close observation and follow-up of patients to evaluate clinical safety, as follows:

- Physical examinations on day 1, 21±2, and 90±7 days, including supine blood pressure, heart rate and neurological examination;
- Collect information on adverse events and bleeding events at each visit after the baseline visit;
- When clinical endpoint events or suspected clinical endpoint events happen, a

follow-up visit should be conducted in time according to Chapter 10.7. Study site should submit data of the event for interpretation and adjudication within 72 hours of the event;

- This study does not require other special laboratory tests. However, if the abnormal laboratory test results are related to the study drug, recording, reporting and handling of adverse events shall be carried out in accordance with the following requirements.

If adverse events occur during the study period, investigators will take appropriate treatment according to the study protocol.

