### **11.2 Definitions of adverse events**

#### **11.2.1 Adverse event (AE)**

Adverse Events, regardless of their relationship to Investigational Product, as long as they occur from the first visit planned in the Clinical Trial Protocol/signature of the informed consent (i.e., occurring during the washout period) to the last visit planned in the protocol, are adverse medical events or deterioration of qualifying event. AEs include symptoms (ie, nausea, chest pain), signs (ie, tachycardia, liver enlargement) and abnormal laboratory results (ie, laboratory or ECG abnormalities). AEs can be classified as serious AEs and non-serious AEs.

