### 11.3 Recording of adverse events

Only some of the non-serious AEs (ie, bleeding events, dyspnea, asthma, renal impairment/increased blood creatinine, bradycardia, increased liver function test indicators, gout/increased uric acid, pneumonia, gynecomastia, abnormal uterine bleeding, malignant tumors) and discontinuations of the study medication due to adverse events (DAEs) will be collected from time of randomization throughout the treatment/follow-up periods to the Study Closure Visit. Other non-serious AEs are up to the investigator to decide whether to collect.

SAE: All SAEs will be collected and recorded.

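### Protocol section 11.5.3 requires study drug to be stopped after any adverse event, which conflicts with sections 7.6 and 7.6.2 (minor)

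*Supplement*

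**What the plan says.** All references are to protocol v1.4.

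- **Section 11.5.3**, on follow-up and risk management: "If an adverse event occurs during the study period, medication will be temporarily discontinued or withdrawn". A list of investigations follows, and then a separate sentence on the care of severe adverse events.
- **Section 7.6**, on discontinuation: "The study drug(s) should be continued whenever possible". Permanent discontinuation is described as a last resort.
- **Section 7.6.1**, on temporary stops: "If the study drugs must be temporarily discontinued, they should be re-started as soon as possible". It names severe thrombocytopenia, GUSTO severe bleeding, need for a prohibited medication, and surgery or procedures, and introduces these as inclusions.
- **Section 7.6.2**, on permanent stops, gives as its fourth example under the investigator's decision: "Adverse events that lead the investigators to believe continued treatment may put the patient at undue risk".
- **Section 11.2.1** defines adverse events without regard to relationship to study drug: "AEs include symptoms (ie, nausea, chest pain), signs (ie, tachycardia, liver enlargement) and abnormal laboratory results".
- **Section 11.3** collects discontinuations due to adverse events under their own label, next to a list of selected non-serious events. For the rest: "Other non-serious AEs are up to the investigator to decide whether to collect".
- **Section 11.5.1** asks the investigator to state, for each event, what was done with study drug. Laboratory, vital-sign and ECG abnormalities count as adverse events only when medically relevant, and leading to discontinuation is one of several ways to meet that test.

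**The concern.** Sections 11.5.3 and 7.6 both tell the site what to do with study drug after an adverse event, and they give different answers. Section 11.5.3 makes the stop automatic. Sections 7.6 and 7.6.2 make it conditional on necessity and on the investigator's view of risk.

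The patients start treatment within 24 hours of a TIA or minor stroke, and the protocol's own background section describes a high early risk of recurrence. Stopping antiplatelet treatment for a trivial event is therefore first a matter of patient safety. It is also a matter of conduct: whichever rule a site follows for a mild event, a monitor could cite the other as breached.

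**Working it through.** No arithmetic applies, so the check is a comparison of the provisions.

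**1. Does anything narrow the sentence in 11.5.3?** Within the section, no. It sets no threshold of severity, requires no causal link and leaves no discretion over whether to act; the only choice is between a temporary stop and withdrawal. Severe events get their own later sentence, so this one cannot be read as confined to them. The definition in 11.2.1 brings in symptoms such as nausea and events unrelated to study drug. Section 11.5.1 takes out laboratory, vital-sign and ECG abnormalities that are not medically relevant, but leaves mild symptoms in.

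**2. A test case.** Take mild, self-limiting dyspnea or minor skin bleeding. Section XI lists both among the side effects of ticagrelor, and both fall within the non-serious events that 11.3 collects.

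| Provision | Instruction for the mild event |
|---|---|
| 11.5.3 | Interrupt or withdraw |
| 7.6 | Continue if possible; permanent stop a last resort |
| 7.6.2, fourth example | Permanent stop only if the investigator sees undue risk |
| 7.6.1 | Event not named, but the list is open; restart promptly after any stop |

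The first row cannot be reconciled with the second. If 11.5.3 is met by withdrawal, it cannot be reconciled with the third either. The fourth row is compatible: a short interruption with a prompt restart would satisfy both 11.5.3 and 7.6.1.

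**3. What do the recording rules assume?** Section 11.5.1 has the action taken with study drug recorded event by event, which presupposes that the action varies. Its list of ways in which an abnormality becomes relevant treats discontinuation as one possibility among several. Section 11.3 keeps a separate category for discontinuations due to adverse events, which would be largely redundant if every event led to a stop. It also leaves some non-serious events to the investigator's choice to collect, and a mandatory stop for an event that need not be collected makes little sense. These are rules of data capture, so they do not contradict 11.5.3, but they fit it poorly.

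**4. Can the effect be sized?** No. The documents give no adverse-event rate, no stopping rate and no time off drug. The sample-size section allows for 5% medication nonadherence, but nothing links the sentence in 11.5.3 to that figure.

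**The case against.** The best reply is that no sensible site would apply the sentence literally. It stands in a section on risk management, not in the section on stopping drug. The work-up that follows it includes arterial blood gas analysis, ultrasound and computed tomography, which suits significant events and not mild nausea. The opening of section XI adds: "If adverse events occur during the study period, investigators will take appropriate treatment according to the study protocol". That leads back to section 7.6, and a dedicated section would normally govern a general remark elsewhere. Protocol v1.0 used a permissive verb at this place. The change between versions is not the fault, but it suggests that the present wording is an editing slip.

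Most of this stands as a reason to rate the point low. It does not remove the conflict, because no text says that 7.6 prevails and 11.5.3 does not refer to it.

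A reader might also infer more than the documents support:

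- **That 7.6.1 is contradicted.** It is not. Its list is open, as is that of 7.6.2, and its call for an early restart is compatible with a brief interruption.
- **That 11.3 contradicts 11.5.3.** It governs what is collected, not when drug is stopped.
- **That any laboratory abnormality would trigger a stop.** Section 11.5.1 limits which abnormalities count as adverse events.
- **That the comparison would be diluted or power lost.** Patients who stop early remain in the full analysis set of SAP v1.3 if they have at least one day of treatment on record, as is ordinary under intention to treat. Dilution would require literal use on some scale, and the documents give no basis for assuming that.

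**Conclusion.** The conflict is real and of minor severity. As written, 11.5.3 requires an interruption or withdrawal after any adverse event. That is incompatible with the instruction in 7.6 to continue whenever possible, and with the undue-risk condition in 7.6.2 for a permanent stop. It also sits badly with 11.5.1 and 11.3.

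The conclusion rests on the wording of protocol v1.4 alone. It does not assume that sites follow the sentence literally, which is unlikely, and it claims no effect on power or on the balance between arms. It matters because the sentence is an operative instruction on dosing in patients at high early risk of stroke, and sites should have one rule.

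**What to change.** Reword the sentence in 11.5.3 along these lines: *if an adverse event occurs, medication may be temporarily discontinued or withdrawn when the investigator judges it necessary, in accordance with sections 7.6, 7.6.1 and 7.6.2.* Notify sites of the change.

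The cost is a one-sentence protocol amendment and a note to sites. Design, sample size and analysis are unaffected.

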## **XII. Ethical standards**

### **12.1 Ethical standards**

This Clinical Trial will be conducted in accordance with the principles laid down by the 18th World Medical Assembly (Helsinki, 1964) and all applicable amendments laid down by the World Medical Assemblies and the ICH guidelines for Good Clinical Practice. Prior to initiating the study, each site will obtain Institutional review board (IRB) or institutional ethics committee (IEC) approval for the protocol, informed consent forms and materials used to recruit subjects. Before each subject is enrolled, the investigator is responsible for fully and comprehensively introducing the purpose, procedures and possible risks of the study to the subject or his/her agent, signing a written informed consent form, and informing the subjects that he has the right to withdraw from this study at any time. The informed consent should be kept as a clinical study document for future reference. The personal privacy and data confidentiality of subjects will be protected during the study process.

### **12.2 Law and regulations**

This Clinical Trial will be conducted in compliance with all international laws and regulations, and Chinese laws and regulations, as well as any applicable guidelines.

### **12.3 Informed consent**

The Investigator/sub-investigator should fully inform the patient of all pertinent aspects of the Clinical Trial, including the written information approved/preferred by the Ethics Committee (IRB/IEC). The Informed Consent Form used by the Investigator for obtaining the patient's informed consent must be reviewed and

approved by the Sponsor and then submitted to the Ethics Committee (IRB/IEC) for approval/favorable opinion.

All participants should be informed to the fullest extent possible about the study, in language and terms they are able to understand. Prior to a patient's participation in the Clinical Trial, Informed Consent Form should be signed and dated by the patient or ~~by~~ the patient's legal representative and ~~by~~ the person who conducted the informed consent discussion. A copy of the signed and dated Informed Consent Form will be provided to the patient.

#### **12.4 Institutional review board/institutional ethics committee (IRB/IEC)**

The Investigator or the Sponsor must submit this Clinical Trial Protocol to the appropriate Ethics Committee (IRB/IEC), and the Ethics Committee is required to forward to the Sponsor a copy of the written approval/favorable opinion signed and dated by the Chairman with Ethics Committee (IRB/IEC) composition. The Clinical Trial (study number, Clinical Trial Protocol title and version number), the documents reviewed (Clinical Trial Protocol, Informed Consent Form, Investigator's Brochure, Investigator's CV, etc.), the list of voting members along with their qualification and the date of the review should be clearly stated on the written (IRB/IEC) approval/favorable opinion.

Investigational Product will not be released at the study site and the Clinical Trial will not start until a copy of signed and dated approval/favorable opinion has been received by the Sponsor.

During the Clinical Trial, any amendment or modification to the Clinical Trial Protocol should be submitted to the Ethics Committee (IRB/IEC). It should also be informed of any event likely to affect the safety of patients or the continued conduct

of the Clinical Trial, in particular any change in safety. All updates to the Investigator's Brochure will be sent to the Ethics Committee (IRB/IEC). If requested, annual progress report, as well as final summary of the Clinical Trial's outcome at the end of the Clinical Trial, will also be sent to the Ethics Committee (IRB/IEC).

### **XIII. Statistical analysis**

The primary null hypothesis of this study is that in patients with TIA or MIS carried *CYP2C19* LOF allele treated with aspirin 75 mg/d, there is no difference in 90-day risk of new stroke (ischemic or hemorrhagic) in those treated with a 3-month regimen of ticagrelor compared with a 3-month regimen of clopidogrel when therapy is initiated within 24 hours of symptom onset.

#### **13.1 Sample size estimation**

Primary null hypothesis: in patients with TIA or minor ischemic stroke carried *CYP2C19* LOF allele treated with aspirin 75 mg/d, there is no difference in 90-day risk of stroke (ischemic or hemorrhagic) in those treated with a 3-month regimen of ticagrelor initiated with a loading dose of 180 mg followed by 90 mg bid compared with a 3-month regimen of clopidogrel initiated with a loading dose of 300 mg followed by 75 mg/d when therapy is initiated within 24 hours of symptom onset.

The minimum necessary sample size in the trial is determined by the requirement to detect the smallest expected, clinically meaningful treatment difference comparing the treatment with placebo. Based on the genetic sub-analysis of the CHANCE study, we presume that the 90-day risk of stroke recurrence in *CYP2C19* loss-of-function allele carriers is about 9.4%, and 6.7% for noncarriers. With the point-of-care identification of the *CYP2C19* loss-of-function allele carriers to assess a proper pharmacogenetic approach for patients with high-risk TIA or MIS, we assumed a 25%

relative risk reduction with alteration from clopidogrel to ticagrelor (90-day risk of stroke recurrence: 7.1%). Considering the potential impact of the interim analyses on the probability of type I error, we adjusted the statistical significance to a 2-sided  $\alpha$  of 0.048. With a sample size of 6,396 patients, we will have 90% power to detect a relative risk reduction (Ticagrelor: loading dose: 180mg, 90mg bid on day 2-90 vs. Clopidogrel: loading dose: 300mg, 75mg qd on day 2-90) of 25% and 5% dropouts (medication nonadherence). Assuming 58.8% prevalence of *CYP2C19* LOF allele carriers in a Chinese population, we projected screening 10,878 patients would be necessary.

### **13.2 Data collection and entry**

Paper-based case report form (CRF) and electronic data capture (EDC) system will be used for data collection and input. All the content required by the protocol in the system must be filled, the unfilled content should be explained, and the reason needs to be marked in the EDC system.

#### **13.2.1 Paper-based CRF filled out by investigator**

Site investigators should use black or blue-black recording pens to fill out the paper-based CRF neatly and clearly to ensure that the data is clear and readable. If the paper-based CRF information needs to be modified, it should not be altered or overwritten. The correct information should be written next to the original information, signed and dated by the person who modified it. The clinical research monitor (CRA) will review the completeness and accuracy of the case report form and guide the investigator to make necessary corrections and supplements.

#### **13.2.2 Data entry to the EDC system by CRC**

After the paper-based CRF is completed, the research coordinator (CRC) will input the content of the paper CRF into the EDC system.

### **13.2.3 Submission to the EDC system after the approval of investigator**

The paper-based CRF ~~is~~ will be submitted after the investigator has approves it. After the data is submitted, all data revisions and feedback are carried out through the EDC system. If the EDC system has submitted a form that needs to be modified, contact the CRA of this center. After the CRA opens the form, the investigator can guide the CRC to modify the data in EDC system.

